### Safety analysis set

The study population will consist of all enrolled patients for whom protocol testing is initiated.

### Data collection

An electronic data capture system will be used to collect the data necessary for this clinical study. The person responsible for preparing the case report form will promptly enter the necessary data into the electronic data capture system and confirm that the information regarding individual research subjects has been recorded correctly. Authentication and access rights to the electronic data capture system will be secured using identifiers and passwords, and encrypted communication will be used for data transmission.

### Statistical analysis plan

Participant characteristics are summarized descriptively. The number of observations, mean, standard deviation, minimum, median, maximum and interquartile range of continuous variables and frequency distributions of categorical variables are calculated.

The proportion of patients with a bowel cleanliness score ≥ 6 is calculated for each group. The difference between groups and 95% confidence interval is estimated using Miettinen-Nurminen method. Noninferiority will be declared when the lower limit of the confidence interval is above the margin. For secondary purpose, we plan to conduct the adjusted analysis using regression models and subgroup analysis restricted to the participants who answer “take more than half” or “take all of the medication.”

Secondary endpoints will bel summarized appropriately and compared between the groups using nonparametric tests. Multiplicity adjustment will not perform for the secondary endpoints.

Frequency distributions of the grade of adverse events will be summarized for each group. Group comparison will be performed using the Fisher’s exact test, if necessary.

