### Randomisation

The principal investigator (or co-principal investigator) will confirm that patients who submit written consent are enrolled as research subjects have fulfilled all the inclusion criteria and none of the exclusion criteria. During this clinical research, patient information will be entered into the registration system (ANCHOR: Shizuoka Cancer Center Clinical Trial Support System; URL: https://www.anchor-scchr.net/). These patients will be registered as research subjects, and randomised by the minimization method. The four allocation adjustment factors will be facilities, age, sex, and inspection objectives.

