#### Sample size calculation

The target number of research participants was 540 (standard group, 270 cases; test group, 270 cases). Based on previous studies, the percentage of the standard group with a bowel cleanliness score ≥ 6 should be approximately 90% [2]. The percentage of the test group with this score is expected to be similar or slightly lower, at 88–90% [2]. The standard cleaning method prior to the current standard bowel cleansing method was 4 L of PEG the day before the colonoscopy; this regimen was considered inferior (inferiority margin, 15%) in terms of good cleaning scores when compared to the split-dose regimen comprising 2 L of PEG plus ascorbic acid. Therefore, a margin of noninferiority of 10% was deemed appropriate. Based on a one-sided alpha error of 2.5%, a beta error of 20%, and a noninferiority margin of 10% for the standard and test groups, the required number of subjects in each group is 255. However, considering a 5% assessment failure rate, the target study population will be 270 subjects in each group. The Farrington–Manning method was used with SAS (version 9.4; SAS Institute, Cary, NC, USA) to calculate the required number of participants [7].

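### Allocation is minimised on four factors but the deciding confidence interval uses none of them; if the factors are prognostic, the interval is somewhat wider than it need be

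*Protocol article*

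**What the plan says.** The Randomisation section states: "These patients will be registered as research subjects, and randomised by the minimization method". It then lists what is balanced: "The four allocation adjustment factors will be facilities, age, sex, and inspection objectives".

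The Statistical analysis plan section gives the deciding analysis: "The difference between groups and 95% confidence interval is estimated using Miettinen-Nurminen method". The decision rule follows: "Noninferiority will be declared when the lower limit of the confidence interval is above the margin". No strata or covariates are named. Adjustment comes next, with a lower rank: "For secondary purpose, we plan to conduct the adjusted analysis using regression models".

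The Sample size calculation section uses the Farrington–Manning method with a standard-group rate of about 90%, a test-group rate of 88–90%, a margin of 10 percentage points, one-sided alpha 2.5% and power 80%. It arrives at 255 per group, raised to 270 for 5% assessment failure. It takes no credit for the minimisation.

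**The concern.** Minimisation makes the arms more alike on the four factors than simple randomisation would. Where a factor affects the outcome, the estimated difference therefore varies less from trial to trial. A two-sample interval that ignores the factors computes its standard error as if that variation were still present. The analysis then does not match the design, and the reported interval is wider than the true uncertainty.

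There is some reason to expect prognostic value. Under Colonoscopy procedures, the examining physician scores cleanliness and the scope model is left open, so facilities may differ in rating and equipment. The Discussion lists indications from positive faecal occult blood tests to surveillance and symptoms. What is at stake is precision that needs no further patients, in a trial planned at 80% power whose registration period had to be extended from 18 to 30 months.

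**Working it through.** **1. The plan's own figure.** Inputs from Sample size calculation: standard 0.90, test 0.88, margin 0.10, one-sided alpha 0.025, power 0.80. The distance from the expected difference to the margin is 0.10 − 0.02 = 0.08.

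- Variance under the expected rates: V1 = 0.90×0.10 + 0.88×0.12 = 0.1956.
- Variance under the null: the restricted maximum-likelihood rates, held 0.10 apart, are 0.9258 and 0.8258, so V0 = 0.9258×0.0742 + 0.8258×0.1742 = 0.2125.
- n = (1.960√V0 + 0.8416√V1)² / 0.08² = 254.3, so 255 per group, as stated.
- 255/0.95 = 268.4, so 269, against 270 stated. This is consistent.
- Power at 255 per group is 80.1%.

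The sample size is therefore that of an unadjusted test.

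**2. Excess width.** The unadjusted Wald half-width at 255 per group is 1.960 × √(0.1956/255) = 5.43 points. In large samples, accounting for factors that explain a share R² of the outcome variance multiplies this by √(1 − R²). The documents do not give R², so a range is shown.

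**3. Power and error.** With se0 = √(0.2125/255) = 0.02887, se1 = √(0.1956/255) = 0.02770 and s = √(1 − R²), and taking balance on the factors as complete:

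- unadjusted power = Φ[(0.08 − 1.960·se0)/(s·se1)]
- adjusted power = Φ[(0.08 − 1.960·s·se0)/(s·se1)]
- unadjusted one-sided type I error = Φ(−1.960/s)

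| R² | Adjusted half-width (points) | Narrower by | Power, unadjusted | Power, adjusted | Type I error, unadjusted |
|---|---|---|---|---|---|
| 0 | 5.43 | 0% | 80.1% | 80.1% | 0.025 |
| 2% | 5.37 | 1% | 80.4% | 80.9% | 0.024 |
| 5% | 5.29 | 2.5% | 80.7% | 82.1% | 0.022 |
| 10% | 5.15 | 5% | 81.4% | 84.2% | 0.019 |
| 20% | 4.86 | 11% | 82.8% | 88.2% | 0.014 |

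**4. Simulation.** 510 evaluable patients were minimised on the four factors. Assumed, because the documents do not say: 10 facilities, 3 age bands, 2 sexes, 3 purposes and a 0.8 biased coin. There were 4,000 trials per setting. The unadjusted Miettinen–Nurminen interval was compared with a risk difference standardised from a logistic model.

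| R² | Coverage, unadjusted | Power, unadjusted / adjusted | Type I error, unadjusted / adjusted |
|---|---|---|---|
| 0 | 95.1% | 81% / 82% | 0.022 / 0.025 |
| 1% | 95.4% | 81% / 83% | 0.027 / 0.030 |
| 4% | 95.5% | 82% / 85% | 0.024 / 0.029 |
| 11% | 96.1% | 83% / 87% | 0.016 / 0.024 |
| 27% | 97.3% | 83% / 93% | 0.014 / 0.034 |

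The Monte Carlo standard error of the type I figures is about 0.0025, so the unadjusted 0.027 at R² = 1% is compatible with 0.025. About 1.4 points of each power gap come from the change of interval method, because that gap is present even at R² = 0. A second simulation with 510 patients and 10 assumed facilities gave, at R² near 10%, power of 83% unadjusted against 85–86% adjusted, and type I error of 0.016 against 0.022–0.023.

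**5. Limits on adjustment.** Expected failures among 510 patients number 255×0.10 + 255×0.12 = 56, or 51 if both arms reach 90%. Cross-classifying the assumed factor levels gives 10×3×2×3 = 180 cells, or 510/180 = 2.8 patients each.

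**The case against.** The strongest reply is that nothing here is invalid. The sample size and the deciding interval are both unadjusted and agree with each other, and the planned test delivers the planned 80%. The error is in the safe direction: a noninferiority claim from the current analysis would not be undermined. The gain rests on a prognostic strength that the documents do not give, and the narrow population (ages 40–69, with constipation and prior abdominal surgery excluded) may weaken the patient-level factors. All of this stands, and it limits the point to efficiency.

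It can also be said that the Miettinen–Nurminen method has a stratified form and that the article does not call its interval unstratified. That is true, but the article sets a separate adjusted analysis apart as secondary, so the unstratified reading is the natural one.

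The remedy has its own risk. In the simulation the adjusted interval ran at a type I error of 0.024 to 0.034 against 0.025. This stands too, and it shapes the fix.

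A reader might go further and infer that the secondary regression will yield an odds ratio, which could not be set against a 10-point margin. The documents do not support this. They name neither logistic regression nor an odds ratio, a logistic model can be standardised to a risk difference, and covariates and scale are details an article commonly leaves to the full plan.

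**Conclusion.** The point holds as a modest loss of efficiency. The deciding interval names none of the four factors used in allocation, and if those factors are prognostic it is too wide: about 1% at R² of 2%, 5% at R² of 10%, nil at zero. The cost in power is at most a few points over that range, about 3 at R² of 10%. Larger gains appear only if the factors explain far more of the outcome than there is reason to assume.

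It would be wrong to infer that the trial is underpowered or that its type I error is inflated: the stated 80% stands and the error is conservative. The direction follows from the design. The size depends on R², the number of facilities and the factor levels, all of which are assumptions here.

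**What to change.** Before unblinding, make the deciding analysis a risk difference that accounts for the minimisation factors, with its lower 95% limit compared with −10 points. Either of two forms would serve:

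- a Miettinen–Nurminen interval stratified by facility alone or by a few coarse strata, with small facilities pooled by a preset rule, and not by the full cross-classification; or
- a standardised risk difference from a main-effects model with a robust, small-sample-corrected standard error.

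Keep the unstratified interval as the sensitivity analysis.

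No new data are needed, since the factors are already used at registration. The costs are a change to the primary-analysis wording in the protocol, and not only in a statistical analysis plan, and the need to write the pooling rule. There is also a risk to guard against: with about 50 to 56 failures, too many terms can make the adjusted interval slightly liberal. The chosen form should therefore be checked by simulation with the actual number of facilities before it is fixed.

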## Methods/design

### Hypothesis

The main research hypothesis of this study is that the test regimen (split-dose SP/MC plus elobixibat) is not inferior to the standard regimen (split-dose of 2 L of PEG plus ascorbic acid) in terms of colon cleanliness. If the superiority of the test regimen compared to that of the standard regimen in terms of acceptability can be demonstrated, then the utility of the test regimen can be demonstrated.

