
### Questionnaire for patients

Patients will be asked to complete a questionnaire that includes the following:

Presence and severity of the following subjective symptoms (assessed using a 5-point scale) before the colonoscopy: abdominal pain, abdominal distension, nausea, vomiting, headache, dizziness, and general fatigue.

The acceptability of the bowel preparation regimen will be determined using a 5-point scale:Was the bowel preparation medication easy to use?Were all bowel preparation medicines administered internally?What is your general impression of the bowel preparation?How did the bowel preparation medicine taste?Did you have a bowel movement promptly after using the bowel preparation medication?Did your stools become clear after using the bowel preparation medication?Did you wake during the night to defecate?Were you able to sleep the day before the examination?Did you have to stop to use a toilet on the way to the examination facility?Do you want to use the same bowel preparation medication for your next colonoscopy?

Presence and severity of subjective symptoms during colonoscopy (assessed using a 5-point scale): insertion pain, abdominal distension, nausea, and vomiting.

Presence and degree of subjective symptoms after colonoscopy (assessed using 5-point scale): abdominal pain, abdominal distension, nausea and vomiting, constipation, diarrhoea, bloody stools, fever, and general malaise.

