#### Secondary endpoints

The secondary endpoints are as follows:Patient acceptability (questionnaire)Adverse eventPolyp/adenoma detection rate and number of polyps/adenomas detectedDegree of bowel cleansing (percentage of BBPS scores > 8)Degree of bowel cleansing (percentage of Aronchik scale scores < 1)Bowel cleansing time (time from the start of bowel preparation until the time when the patient is ready for the examination)

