## Discussion

This study aims to evaluate the degree of bowel cleansing and acceptability of a new regimen comprising split-dose SP/MC plus elobixibat hydrate and compare it with the standard regimen comprising split-dose PEG plus ascorbic acid by performing a randomised comparison. The primary endpoint is the degree of bowel cleansing according to the BBPS score of the noninferior design. The secondary endpoint is acceptability, which will be determined using a questionnaire regarding the superiority of the design. If the test regimen is not inferior to the standard regimen according to the primary endpoint, and if the superiority of the test regimen compared to that of the standard regimen in terms of acceptability can be demonstrated, then the utility of the test regimen can be demonstrated.

PEG is the most commonly recommended solution for bowel preparation according to the guidelines of Western countries because of its colon-cleansing effectiveness [2, 3]. Recently, a split dose has been recommended not only for colon cleansing but also for improving the adenoma detection rate [8]. However, PEG has some problems in terms of patient acceptability, such as the need for a large dose and its flavour.

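### The utility conclusion needs superior acceptability, but acceptability is ten unadjusted questionnaire items with no stated rule for deciding superiority

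*Protocol article*

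**What the plan says.** The Hypothesis section puts forward noninferior cleansing as the principal hypothesis and then adds a second condition: "If the superiority of the test regimen compared to that of the standard regimen in terms of acceptability can be demonstrated", utility follows. The Discussion makes the pairing explicit. It opens with "If the test regimen is not inferior to the standard regimen according to the primary endpoint", adds superiority on acceptability, and concludes "then the utility of the test regimen can be demonstrated". It also gives acceptability a superiority aim: "The secondary endpoint is acceptability, which will be determined using a questionnaire regarding the superiority of the design".

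The Questionnaire for patients section says "The acceptability of the bowel preparation regimen will be determined using a 5-point scale" and lists ten questions: ease of use, whether everything was taken, general impression, taste, promptness of the bowel movement, clearness of stools, waking at night, sleep, toilet stops on the journey, and willingness to use the same preparation again. It gives no total score and no key item. The Secondary endpoints list says only that acceptability comes from the questionnaire.

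The Statistical analysis plan section says that secondary endpoints are "compared between the groups using nonparametric tests", and then: "Multiplicity adjustment will not perform for the secondary endpoints".

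**The concern.** The article gives acceptability two roles that do not fit together. In the Hypothesis and Discussion it is one of two conditions for the trial's conclusion. In the analysis section it is one of several secondary endpoints, tested without error control. Forgoing adjustment is a reasonable choice when secondary results are only supportive. It is a poor one when a secondary result has to be demonstrated before the main conclusion can be drawn.

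Mixed results across the ten items are foreseeable from the article itself. The Background reports that sodium picosulfate/magnesium citrate did better than polyethylene glycol on ease, impression, taste and volume. The Abstract and Discussion describe its defaecation response as slower. The questionnaire covers both kinds of property, so some items may favour the test regimen and others the standard one. Some items are also not plainly acceptability: clear stools is a patient's view of cleansing, and whether everything was taken is adherence. Nothing in the article says what would then count as superiority. If the deciding item is picked after the results are seen, the utility claim has no known error rate.

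**Working it through.** **The plan's own figure.** The only error rates in the article belong to the primary endpoint. Inputs from Sample size calculation: standard 90%, test 88% (the lower end of the stated 88–90%), margin 10 points, one-sided alpha 2.5%, power 80%, Farrington–Manning method.

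- Restricted rates under the null: 0.9258 and 0.8258, so v0 = 0.9258 × 0.0742 + 0.8258 × 0.1742 = 0.2125.
- Variance term under the alternative: v1 = 0.90 × 0.10 + 0.88 × 0.12 = 0.1956.
- Distance from the margin: 0.10 − 0.02 = 0.08.
- n = (1.960 × √0.2125 + 0.842 × √0.1956)² / 0.08² = 254.3, so 255 per group, as stated.
- 255 / 0.95 = 268.4, so 269; the plan's 270 agrees.

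The primary calculation reproduces. Acceptability plays no part in it.

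**False-positive rate for acceptability.** The article states no figure, so three assumptions are needed:

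1. Each item is tested at two-sided 5%, which is 2.5% in the direction favouring the test regimen.
2. The regimens do not truly differ on any item.
3. One significant item favouring the test regimen is taken as superiority.

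For independent items: 1 − 0.975^10 = 0.224. For correlated items, ten equally correlated normal test statistics were simulated (400,000 draws).

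| Correlation between items | Chance of at least one item favouring the test regimen |
|---|---|
| 0 | 22.4% |
| 0.3 | 17.9% |
| 0.5 | 14.4% |
| 0.7 | 10.7% |
| 0.9 | 6.4% |
| One prespecified test | 2.5% |

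**Sensitivity to the number of items.** With nine items (for example, leaving out completeness of intake) the rates are 20.4% if independent, 13.5% at correlation 0.5 and 6.2% at 0.9. With eight independent items, 1 − 0.975^8 = 18.3%.

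**Sensitivity to the rule.** If all ten items had to be significant in favour of the test regimen, the rate would be below 0.6% even at correlation 0.9. The error rate therefore runs from under 1% to over 20%, depending on a rule that the article does not give.

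**After a correction.** One prespecified item or score gives 2.5%. Bonferroni over ten items (two-sided 0.005 each) gives 2.5% at correlation 0, 2.0% at 0.5 and 0.8% at 0.9. With no true difference on any item, Holm has the same chance of at least one false claim, because its first step is the Bonferroni test.

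**The case against.** The strongest reply is that this is ordinary detail for a full protocol or analysis plan, neither of which is shown. Scoring, the key item and the testing order may all be defined there. That is fair as far as missing detail goes. It does not cover the sentence declining adjustment, which is a stated decision and conflicts with the role that the same article gives acceptability.

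A second reply is that acceptability is listed as secondary, that the only formal success rule concerns the primary endpoint, and that the utility sentences are interpretation. This stands in part: the article never calls acceptability confirmatory. But it says twice that utility is demonstrated when superiority is shown. If those sentences are only interpretation, they should be worded that way.

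A reader might also infer more than the documents support:

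- That the relevant error is 40% (1 − 0.95^10). That figure counts items favouring the standard regimen, which cannot support a utility claim.
- That the plan lets any single item decide. It states no rule; the any-item rule is an assumption used to size the problem.
- That no test is specified. A class of tests, nonparametric, is named and suits 5-point items. What is absent is the deciding item, score or rule.
- That the utility claim is uncontrolled in every situation. It also needs noninferiority at one-sided 2.5%, so if the test regimen is truly worse by the full margin, a false utility claim is held to about 2.5% whatever the questionnaire shows. The inflation matters when the regimen is truly noninferior and has no acceptability benefit.
- That alpha must be split between the primary endpoint and acceptability. It need not be, because both must succeed.

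Independence between answers from one patient about one preparation is also implausible, so 22% is the upper end of the range shown.

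**Conclusion.** The point holds as a conflict between a stated conclusion and a stated analysis policy. The article rests the utility conclusion partly on superior acceptability, measures acceptability with ten items, gives no rule for deciding, and declines adjustment. Once noninferiority is met and with no true acceptability difference, the chance of a false claim for the test regimen would be about 6% to 22%, or 11% to 14% at correlations of 0.7 to 0.5, against 2.5% for a single prespecified test. These figures depend on the assumed 5% per item, the assumed correlations and the any-item rule; a stricter rule would give a much lower rate. The noninferiority comparison, its margin and the sample size are not affected.

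**What to change.** Choose one of these, and record the choice before any between-group questionnaire data are examined. That is the right cut-off because, under Blinding, the patients who answer the questionnaire know their regimen.

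- **One key endpoint.** Name a single acceptability measure, such as the willingness-to-reuse question already collected or a prespecified total score. Give it a named nonparametric test (for example Wilcoxon rank-sum) at two-sided 5%, carried out only if noninferiority is met. State that the utility claim needs both results. Report the other items descriptively with confidence intervals.
- **Adjustment across items.** List the items that count as acceptability, apply Holm across them, and say how many must favour the test regimen and what follows if others favour the standard. Report any items outside the list descriptively.
- **Softer wording.** Keep the no-adjustment policy and change the Hypothesis and Discussion so that acceptability is supportive only. If comparative questionnaire data have already been seen, only this option remains.

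The cost is a wording change, with no new data and no change in sample size. With one key endpoint, the other items can no longer support a confirmatory claim. With Holm, each item faces a stricter threshold, starting at 0.05 / 10 = 0.005 if all ten are kept.
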